### Trial coordination and implementation

Each medical and paramedical team in the eight participating reference centres and in the SOS-HAE call centre is trained in protocol implementation and data collection. The electronic case report form (eCRF) was developed using CleanWEB™ (a centralised, secure, interactive web response system edited by Telemedicine Technologies and accessible from each study centre). In accordance with French law, the eCRF and database were validated by the CCTIRS (*Comité consultatif sur le traitement de l’information en matière de recherche dans le domaine de la Santé -* Advisory Committee on Information Processing in Healthcare Research) and by the CNIL (*Commission Nationale de l’Informatique et des Libertés* - French Data Protection Authority).

### Blinding

Physicians and nurses could not be blinded to the intervention given its nature, but patients are blinded to the intervention by Zelen’s method (pre-randomisation consent). The single-blind procedure is partially counterbalanced by the objective nature of the primary outcome measure [19]. The analysis will be blinded to group allocation.

### Outcome measures

#### Primary outcome

The primary outcome is the number of admissions for angioedema attacks per patient per year over a 2-year period. The number of admissions for angioedema attacks is measured from the randomisation date until the end of follow-up or death. For patients discharged alive, information on the primary outcome will be collected by phoning the patients. All admission observation charts are collected and collated.

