**Methods/design:**

This prospective, cluster-randomised, single-blind, parallel-group, multicentre trial evaluates the morbidity and consequent socio-economic costs of the management of patients experiencing an HAE attack by a dedicated call centre as compared to usual practice. The trial aims to recruit 200 patients. Patients in the intervention arm are provided with an SOS-HAE card with the call centre’s freephone number that they can access in the case of an attack. The centre’s mission is to provide recommended expert advice on early home treatment. The centre can route the call to a local emergency medical service with competency in HAE management or even arrange for the drugs needed for the specific treatment of an HAE attack to be sent to the emergency department of the local hospital. The primary outcome measure is the number of hospital admissions for an HAE attack. Each patient will be followed up every 2 months for 2 years. The study has been approved by the ethics committee (*Comité de Protection des Personnes d’Ile de France 10*; registration number: 2012-A00044-39; date of approval: 19 January 2012).

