### Randomisation

The randomised units are the reference centres (clusters) with randomisation stratified according to the number of eligible HAE patients by reference centre. Using permuted blocks of 4, we randomly assigned reference centres (not patients) to the intervention or to usual practice (1:1 ratio).

A modified version of Zelen’s method involving a two-step informed consent process was used for randomisation and inclusion [18]. Eligible patients were first invited to participate in a cohort study but without being informed of the nature of the study arms. Patients who agreed to participate in the study signed the first consent form. This was followed by verification of eligibility (compliance with inclusion/exclusion criteria) and centre randomisation. The patients in each centre were then offered inclusion in the arm assigned to their centre but without being informed of the nature of the other arm. Patients who agreed to be included signed the second consent form. The patient inclusion day is study day zero (D0).

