### Intervention arm

All patients in the intervention arm are given an SOS-HAE card indicating what to do in the case of an attack: *“On attack onset and before taking any drugs, call the freephone number [name]*”. The physicians receiving the call at the call centre (open 24/7/365) have received special training as well as instruction sheets on emergency HAE management according to attack severity (Table 1). They can prescribe home treatment or route the call to a local EMS team with competency in HAE management. They can also make arrangements for specific drugs to be sent to the ED of the patient’s local hospital.

**Table 1 Tab1:** Treatment recommendations

Treatment	Recommendations
Vital distress	- Immediately and as soon as possible:
	- Administer icatibant (Firazyr®): 30 mg subcutaneously or
	- plasma-derived C1-INH (Bérinert®): 20 UI/kg intravenously
	- Switch the call to the local SAMU to send French EMS
	- Gain control of upper airway
Severe attacks	- Immediately and as soon as possible:
Laryngeal	- Administer icatibant (Firazyr®): 30 mg subcutaneously or
Facial	- plasma-derived C1-INH (Bérinert®): 20 UI/kg intravenously
Abdominal	- If treatments are unavailable at home, switch the call to the local SAMU to send an ambulance headed towards a hospital with specific treatments available or being able to get them by French EMS
	- Gain control of upper airway
Non-severe attacks (members, genitals)	- Tranexamic acid: 1 g/6 h except for patients who are breastfeeding or have thromboembolic pathology
Surveillance in all cases	Monitoring by phone 30 min, 1 h, 4 h, 12 h and 24 h after the beginning of the attack
	Advice to call back SOS-HAE call centre in case of secondary worsening

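### Admissions are counted from the randomisation date, which belongs to the centre, while each patient's day zero is the later inclusion day; any interval between the two dilutes the treatment contrast

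*Protocol article*

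**What the plan says.** All references are to the protocol article.

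- **Outcome measures, Primary outcome.** The endpoint is a rate over two years: "The primary outcome is the number of admissions for angioedema attacks per patient per year over a 2-year period". The counting rule follows: "The number of admissions for angioedema attacks is measured from the randomisation date until the end of follow-up or death".
- **Randomisation.** The unit is the centre: "we randomly assigned reference centres (not patients) to the intervention or to usual practice (1:1 ratio"). Patients first consent to a cohort study. Then: "This was followed by verification of eligibility (compliance with inclusion/exclusion criteria) and centre randomisation". After that: "The patients in each centre were then offered inclusion in the arm assigned to their centre". Those who accept sign a second consent form, and the patient's clock is set: "The patient inclusion day is study day zero (D0").
- **Intervention arm.** Exposure comes with membership of the arm: "All patients in the intervention arm are given an SOS-HAE card indicating what to do in the case of an attack".
- **Data collection and follow-up, Medical data.** Baseline items are collected on D0. Attack and admission data are then collected at each attack and at two-monthly contacts for two years.
- **Abstract, Methods/design.** "Each patient will be followed up every 2 months for 2 years".

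**The concern.** When individuals are randomised, counting from randomisation is routine, because that date and the start of follow-up nearly coincide. Here no patient has a randomisation date of their own. The only one described is the centre's, and every patient at a centre shares it. The article places inclusion after it.

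An analyst who follows the Primary outcome sentence literally would count admissions, and presumably person-time, from a date before the patient was offered the arm. In that stretch an intervention patient is not in the arm and, on the order of events given, cannot yet hold the card. Both arms are then under usual practice, so if the call centre works, the added time pulls the observed difference towards zero. An analyst who follows the D0 definition would obtain a different count from the same data. The primary result should not depend on which sentence is followed.

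**Working it through.** **Order of events (Randomisation section).** First consent → eligibility check → centre randomisation → offer of the assigned arm → second consent → inclusion = D0. The counting rule starts at the third step and the patient's clock at the last. With 200 patients in eight centres there are on average 200 / 8 = 25 patients per centre date. Unless all patients at a centre are included on the day it is randomised, the gap is above zero for some of them and varies between patients.

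**Inputs.** From Sample size calculation: 88 % versus 68 % (a 20-point difference), design effect 1.4, 100 patients per arm, 85 % power, two-sided 5 %. From Primary outcome: a 24-month window. The gap g between centre randomisation and D0 is not in the article; 0 to 12 months is assumed here.

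**The plan's own figure.** Unpooled two-proportion formula:

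n = (1.96 + 1.036)² × (0.88 × 0.12 + 0.68 × 0.32) / 0.20² = 72.5 per arm; 72.5 × 1.4 = 101.6.

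This matches the stated 100 per arm to within two patients.

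**Dilution.** Give intervention patients the control rate during the gap and the planned rate afterwards.

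- Window A, 24 months counted from centre randomisation: difference = 20 × (1 − g/24).
- Window B, the gap plus 24 months after D0: difference = 20 × 24/(24 + g).

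Both are needed because the article does not say which window the literal rule implies.

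Power uses the pooled two-proportion formula with effective n = 100/1.4 = 71.4 per arm:

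power = Φ{[d√n − 1.96 √(2p̄(1 − p̄))] / √(p₁(1 − p₁) + p₂(1 − p₂))},

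where d = p₁ − p₂ and p̄ is the mean of the two proportions.

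| Gap g (months, assumed) | Difference, A (points) | Power, A | Difference, B (points) | Power, B |
|---|---|---|---|---|
| 0 | 20.0 | 83 % | 20.0 | 83 % |
| 1 | 19.2 | 80 % | 19.2 | 80 % |
| 3 | 17.5 | 74 % | 17.8 | 75 % |
| 6 | 15.0 | 62 % | 16.0 | 67 % |
| 12 | 10.0 | 36 % | 13.3 | 53 % |

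The starting value is 83 % rather than 85 % because the pooled formula is slightly stricter than the unpooled one that reproduces the plan's figure.

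The power columns are illustrative only. The sample size inputs describe a proportion with ED visits or admissions, whereas the primary outcome is a count of admissions. The shrinkage of the difference does not depend on the power formula, but it does depend on the assumed gap and on equal rates in the two arms before D0.

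**The case against.** **The gap may be short.** By the time a centre is randomised, its patients have, as written, already given first consent and been screened. Only an offer and a signature remain, which fits days as well as months. This stands, and the size is conditional on it. A reader might infer gaps of many months from the ethics approval (January 2012) and the end of recruitment (June 2014). Neither is a centre randomisation date or a first inclusion date, so they do not bound the gap.

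**Counting from randomisation is the intention-to-treat convention.** Intention to treat fixes which patients are analysed and in which arm. Starting at D0 drops no included patient and moves none between arms. One part of the objection does stand: D0 falls after allocation is known to unblinded staff, so its timing could differ by arm.

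**The authors may simply mean inclusion.** This is possible. The article is condensed, the design figure and flowchart are not shown, and the full protocol may define the date. The sentence as printed still names a date that patients do not have.

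**Stronger readings that the article does not support.**

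- That the rule contradicts the two-year period: two years counted from centre randomisation would satisfy both sentences of the Primary outcome section, and a rate per year tolerates unequal durations.
- That no prospective data exist before D0: patients have already consented to a cohort, and the outcome is gathered by telephone and from admission charts. Nothing rules out capture before D0, although the described schedule starts there.
- That having to survive to inclusion biases the comparison: this applies to both arms, and no difference between them is shown.

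**Conclusion.** The point holds as an unreconciled pair of time origins. The count starts at a centre-level date, while the patient's day zero and the described data collection start at inclusion. If the literal rule is applied and the intervention works, any gap moves the result towards no difference. The direction follows from the order of events, taking rates before D0 as equal in the two arms.

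The size is unknown. It is negligible for a gap of days. Under the assumed fixed 24-month window, the planned difference falls from 20 points to about 19.2, 17.5 and 15.0 points at 1, 3 and 6 months. The 20 is a difference in percentage points (88 % to 68 %), not a 20 % relative reduction; the relative reduction is 20/88, about 23 %.

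A reader might also infer that unequal gaps bias the comparison between arms. They could, particularly with only eight randomised centres, but the article gives no gap by centre or arm, so this remains a possibility and not a finding.

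**What to change.** In the Primary outcome section, replace the randomisation date as the starting point with: from D0 (patient inclusion) to D0 + 24 months, death or withdrawal, whichever is first. Use that same interval as each patient's person-time in both arms, so that numerator and denominator match, and make the wording agree with the Randomisation and Medical data sections. Settle this before the blinded analysis begins.

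The cost is small. It is one sentence and needs no new outcome data, because D0 is already the protocol's anchor. Admissions between centre randomisation and D0 would no longer count. Because D0 comes after staff know the allocation, report the interval from centre randomisation to D0 by arm, so that readers can see whether inclusion was delayed more in one arm than in the other.

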#### Secondary outcomes

Secondary outcomes are the number of admissions for a cause other than an angioedema attack per year over a 2-year period, mortality from an angioedema attack, mortality from another cause, number of ICU admissions per year, number of ED admissions per year, number of hospital stays, number of intubations per year, number of interventions by EMS, number of working days lost and their duration, costs of patient care and SF-36 score.

#### Definitions

An admission is defined as a hospital stay >12 hours as an inpatient. An ED visit is defined as a consultation in the ED without admission (stay ≤24 hours).

### Sample size calculation

The aim of this study is to demonstrate a difference in outcome between a methodical management strategy and usual practice. Our primary hypothesis is that an SOS-HAE call centre might benefit patients suffering from an angioedema attack. The sample size calculation is based on the primary outcome, i.e. on the number of admissions for angioedema attacks.

A recent study involving 193 patients with HAE in France reported a rate of approximately 8 attacks/year/patient with approximately 11 % of patients coming to the ED or being admitted to hospital (i.e. an estimated 88 % per year). We hypothesise that implementation of the SOS-HAE call centre management strategy should reduce this rate by 20 %, resulting in a rate of 68 % of ED visits or admissions per year over a 2-year period. If we consider the design effect due to cluster randomisation as relatively low (1.4), the estimated required sample size is 100 patients/arm for 85 % power and a 5 % alpha risk (two-sided comparison).

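### The stated 85 % power is computed for ED visits or admissions combined and is not supported for the declared primary outcome, which counts admissions only

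*Protocol article*

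**What the plan says.** The Sample size calculation section names its basis: "The sample size calculation is based on the primary outcome, i.e. on the number of admissions for angioedema attacks".

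The figures in the next paragraph are of another kind. The control rate comes from a French cohort with "approximately 11 % of patients coming to the ED or being admitted to hospital (i.e. an estimated 88 % per year" as its summary. The call centre "should reduce this rate by 20" %, "resulting in a rate of 68 % of ED visits or admissions per year over a 2-year period". With a design effect of 1.4, two-sided alpha of 5 % and 85 % power, the section arrives at 100 patients per arm.

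Elsewhere in the article:

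- Primary outcome: "The primary outcome is the number of admissions for angioedema attacks per patient per year over a 2-year period".
- Definitions: an admission is an inpatient stay of more than 12 hours, and "An ED visit is defined as a consultation in the ED without admission".
- Secondary outcomes: ED use is listed separately from admissions.
- Background and Discussion: the same 11 % is described as patients who went to the ED, with no mention of admission.

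**The concern.** By the article's own definitions, an ED visit without admission cannot count towards the primary outcome, yet such visits are part of the rates used for planning. Admissions are only a part of the planned events, and the size of that part is nowhere stated.

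The power for the outcome that carries the trial's conclusion is therefore unknown. If the call centre has the same relative effect on admissions as on the combined event, the absolute difference shrinks with the baseline and power falls. A null result on admissions could then be read as evidence against the call centre from a trial with 85 % power, when the trial did not have that power for admissions.

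**Working it through.** **Inputs from the Sample size calculation section:** p1 = 0.88, p2 = 0.68, design effect 1.4, 100 per arm, two-sided alpha 0.05, power 0.85. No dropout allowance is stated.

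**Step 1: reproduce the plan's figure.** Two proportions, unpooled variance:

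n = (1.96 + 1.036)² × [p1(1 − p1) + p2(1 − p2)] / (p1 − p2)²

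= 8.978 × (0.1056 + 0.2176) / 0.04 = 72.5 per arm; × 1.4 = 101.6, so 102.

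This is within 3 % of the stated 100. The arcsine formula gives 103 and the pooled formula 107. Conversely, 100 / 1.4 = 71.4 effective patients per arm. The pooled power formula is

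power = Φ{ [|p1 − p2| √n − 1.96 √(2p̄(1 − p̄))] / √(p1(1 − p1) + p2(1 − p2)) }, with n = 71.4 and p̄ the mean of p1 and p2.

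For 0.88 vs 0.68 it gives Φ[(1.690 − 1.96 × 0.5858) / 0.5685] = Φ(0.954) = 83 %. The stated size therefore follows from the combined rates. The comparator for what follows is 83 %, from the same formula.

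**Step 2: admissions only.** The article gives no admissions rate for this population. Let s be the share of the combined events that are admissions (an assumption), so the control rate is 0.88 × s. The article gives one figure that bears on s: in another retrospective study, 59 % of those presenting at the ED were admitted (Discussion). It appears below as one value in a range.

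The effect can be carried over in two main ways: keep the ratio 68/88, or keep the 20-point fall that the protocol applied.

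| s | Control rate | Same ratio: intervention rate | Power | 20-point fall: intervention rate | Power |
|---|---|---|---|---|---|
| 1.0 (as planned) | 88.0 % | 68.0 % | 83 % | 68.0 % | 83 % |
| 0.9 | 79.2 % | 61.2 % | 66 % | 59.2 % | 74 % |
| 0.8 | 70.4 % | 54.4 % | 51 % | 50.4 % | 69 % |
| 0.7 | 61.6 % | 47.6 % | 39 % | 41.6 % | 67 % |
| 0.59 | 51.9 % | 40.1 % | 29 % | 31.9 % | 68 % |
| 0.5 | 44.0 % | 34.0 % | 23 % | 24.0 % | 72 % |

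Worked at s = 0.59:

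- Same ratio: Φ[(0.997 − 1.96 × 0.7049) / 0.6999] = Φ(−0.549) = 29 %.
- 20-point fall: Φ[(1.690 − 1.96 × 0.6978) / 0.6833] = Φ(0.472) = 68 %.
- A 20 % relative cut (51.9 % to 41.5 %): 24 %.

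**Step 3: when would the planned power be reached?** With the ratio kept, at no s below 1. With the 20-point fall kept, power rises again at low baselines: 79 % at s = 0.4, about 85 % at s = 0.35 and 91 % at s = 0.3. At s = 0.35 the control rate is 30.8 %, and a 20-point fall is a relative reduction of 20 / 30.8 = 65 %. At s = 0.3 it is 20 / 26.4 = 76 %.

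**The case against.** The mismatch itself has no good defence. It is a statement contradicted by the figures beside it, so the condensed form of a journal article does not explain it. The objections to its size are sound and limit what can be claimed.

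- **A reader might infer that the true power is about 30 %.** That figure needs both s = 0.59 and the ratio 68/88. The 59 % comes from a different cohort and is a share of ED presenters. The combined rate as worded could also include direct admissions, so s may be higher. The ratio 68/88 is a 22.7 % relative cut, which is neither the 20 % stated nor the 20 points applied. With the 20-point fall kept, power at the same s is 68 %, about 15 points below the 83 % comparator.
- **A reader might infer that power is overstated whatever the effect.** This is certain only for a fixed relative effect. With a fixed 20-point fall, power reaches the planned level once s is about 0.35 or less. The exception stands arithmetically, but it needs relative reductions of about 65 % or more, which the protocol nowhere proposes.
- **A Poisson calculation over 2 years gives 31 % at s = 0.59 with the same ratio.** It does not isolate this problem: the same model with design effect 1.4 gives only 48 % for the combined 0.88 vs 0.68. Much of the apparent fall comes from changing the model, so the figure is not used here.
- **Recruitment was completed in June 2014 (Trial status).** The number of patients is therefore settled. That limits the remedy to the text and leaves the error in the stated power.

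**Conclusion.** The point holds as an internal contradiction with a real consequence. The 85 % power at 100 per arm was derived for ED visits or admissions and is not supported for admissions for angioedema attacks.

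The mismatch is certain; the size of the power loss is not, because it depends on an admissions share that the article does not give and on how the effect is carried over. For shares of 0.5 to 0.9, power is 23 to 66 % with the ratio kept and about 67 to 74 % with the 20-point fall kept, against 83 % for the planned rates by the same formula. All these values treat the yearly rates as proportions and take the design effect of 1.4 as given, as the protocol appears to do. No single replacement figure, such as about 30 %, is supported.

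**What to change.** In the Sample size calculation section:

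1. State that 88 % and 68 % describe ED visits or admissions combined, and remove the claim that they describe the primary outcome.
2. Redo the calculation from an admissions-only control rate with its source, and state the effect as either relative or absolute.
3. Replace the 85 % with the power that 200 patients give for admissions, shown over a range of assumed admission shares.

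Keep admissions as the primary outcome; no added patients are needed. Naming the combined ED-visit-or-admission rate as a secondary outcome is optional. Both components are already collected (Data collection and follow-up, Medical data), so it would need no new data.

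The cost is a change of text, a search for an admissions-only rate and a less favourable power statement.

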## Background

Hereditary angioedema (HAE) is a rare disease. Worldwide prevalence ranges from 1/50,000 to 1/100,000 [1]. The form exhibiting C1 inhibitor (C1-INH) deficiency is an autosomal dominant disorder, although 25 % of cases are due to a spontaneous mutation in individuals with no family history of the disease [2, 3]. Patients with C1-INH deficiency may have type I or type II HAE [2, 3]. Patients with a family history of angioedema but with normal C1-INH levels may have a mutation of the gene encoding human coagulation factor XII (FXII-HAE) [2].

HAE attacks are characterised by recurrent subcutaneous swelling without itching lasting 48 to 72 hours [3, 4]. By far the most common sites of attacks are the extremities and abdomen, each accounting for nearly half of all attacks [5]. Abdominal attacks can cause severe pain and third-space fluid accumulation with resultant hypotension [5, 6]. Moreover, more than half of all HAE patients experience at least one laryngeal attack during their lifetime with the associated risk of asphyxiation [7]. Despite the availability of guidelines on specific treatments for HAE attacks, morbidity and mortality rates remain substantial [2, 3, 8].

The management of patients with HAE is shifting towards self-treatment of attacks at home with fewer visits to the hospital emergency department (ED) and fewer admissions [9, 10]. Even so, in a recent retrospective study of 193 HAE patients with 8 attacks/patient/year, approximately 11 % of patients visited the ED [11]. Moreover, according to a prospective observational study including 29 HAE patients, laryngeal and facial edemas are independent risk factors associated with hospital admission, and this is not avoided by early ED arrival [12]. A prospective study on the impact of measures, in particular specific home treatments, that might shorten the time from attack onset to first contact with a healthcare professional is required [12].

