## Discussion

Key priority issues in HAE management are reducing morbidity and mortality rates and socio-economic costs [2]. No study has ever been conducted to determine whether a central dedicated call centre for HAE attacks would reduce morbidity and the socio-economic impact of the disease.

The indications for the specific treatment of HAE attacks are well established. Plasma-derived C1INH and icatibant are the undisputed emergency drugs for life-threatening cases (laryngeal involvement), abdominal attacks and cases with facial involvement [2, 3, 20, 21]. Early home treatment is recommended [2, 15]. HAE patients trained in icatibant self-administration can recognise HAE attacks and decide when to inject [22], thereby avoiding hospital admission [12]. In an evaluation of the feasibility and efficacy of plasma-derived C1-INH in 31 patients with HAE, the time from attack onset to start of treatment was significantly shorter after than before training in self-injection [23]. Nevertheless, morbidity remains high in these patients. In one retrospective study, 73 patients (16 %) presented at the hospital ED with an attack and 59 % were admitted to hospital [13]. In another, 21 patients (11 %) presented at the hospital ED with an attack [11]. According to a recent prospective study, most of these patients visited the ED because they were short of medication or because they were unaware that emergency treatment could be self-administered. Our prospective controlled cluster-randomised trial would enable evaluation of the impact of a measure (dedicated call centre) that might shorten the time from attack onset to first contact with a healthcare professional.

HAE is a considerable economic burden both to the healthcare system and to HAE patients and their families [13]. Reducing the number of hospital admissions might help reduce this burden. We hypothesise that the use of a dedicated call centre providing expert advice for HAE might significantly reduce the number of admissions (morbidity rate) and thus the socio-economic costs associated with the disease.

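### The sample size treats 8 attacks × 11% of patients = 0.88 as a binomial proportion, so the stated 85% power is not supported for a primary outcome that counts admissions

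*Protocol article*

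**What the plan says.** Under Sample size calculation, the protocol article ties the calculation to the primary endpoint: "The sample size calculation is based on the primary outcome, i.e. on the number of admissions for angioedema attacks". Under Primary outcome, that endpoint is a count per unit of time: "The primary outcome is the number of admissions for angioedema attacks per patient per year over a 2-year period".

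The planning figures come from one earlier French study: "A recent study involving 193 patients with HAE in France reported a rate of approximately 8 attacks/year/patient". The paragraph pairs this attack rate with 11%, described as a share "of patients coming to the ED or being admitted to hospital (i.e. an estimated"; the annual figure it supplies is 88%. The effect is then set: "We hypothesise that implementation of the SOS-HAE call centre management strategy should reduce this rate by". The size given for this reduction is 20%, and the paragraph says it leads to 68% of ED visits or admissions per year. With a design effect of 1.4, it arrives at 100 patients per arm for 85% power at a two-sided 5% level.

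The same 11% appears twice more. The Background describes it as a share "of patients visited the ED", in a study of 193 patients with 8 attacks per patient per year. The Discussion, citing the same reference, gives the number behind it: "In another, 21 patients" (11 %) presenting at the ED.

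**The concern.** Two quantities with different units appear to have been multiplied. A share of patients times attacks per patient-year is neither an event rate nor a proportion of patients. Had the 11% been a share of attacks, the product would be a mean of 0.88 events per patient-year. Such a mean can exceed 1 and has a count's variance; it does not say that 88% of patients have an event.

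This matters because a binomial variance near 0.9 is small. If 0.88 is really a mean count, the variability is larger and the required number of patients rises. This paragraph is the article's only justification for 200 patients. A null result read against a claimed 85% power could be taken as evidence that the call centre does not work when the trial may not have been sized to show it.

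Two related points bear on the same paragraph. The stated 20% reduction does not lead from 88% to 68%. And the planning event, ED visits or admissions, is wider than the primary outcome, which is admissions only.

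**Working it through.** **Inputs.** From Sample size calculation: 8 attacks per patient-year, 11%, 88%, 68%, design effect 1.4, 100 per arm, 85% power, two-sided 5%. From Randomisation: 1:1 allocation. From Background and Discussion: 21 patients and 193 patients. From Primary outcome: 2 years of counting. The normal quantiles are 1.960 and 1.036, so (1.960 + 1.036)² = 8.98. At 100 per arm the effective size is 100/1.4 = 71.4 per arm.

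**Step 1. Unit of the 11%.** 21/193 = 10.9%, a share of patients. The protocol does not write out how 88% arises, but 8 × 0.11 = 0.88 is the only evident route.

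**Step 2. Reproducing the stated size.** For two independent proportions with unpooled variance:

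n = 8.98 × (0.88 × 0.12 + 0.68 × 0.32) / 0.20² = 8.98 × 0.3232 / 0.04 = 72.5 per arm

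72.5 × 1.4 = 101.6 per arm, against the stated 100. Power at 71.4 effective patients per arm is Φ(0.20 / √(0.3232/71.4) − 1.96) = Φ(1.01) = 84.5%. The arcsine formula gives 102.6 per arm. The stated size and power therefore follow from using 88% and 68% as proportions.

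**Step 3. The stated effect.** 0.88 × 0.80 = 0.704. The printed 68% is a cut of 20 points, or 1 − 0.68/0.88 = 22.7% relative. Still as proportions, 88% vs 70.4% needs 127 per arm (unpooled) to 132 per arm (pooled); power at 100 per arm is 76% and 74% respectively.

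**Step 4. Illustration on the count scale.** Three assumptions are needed: 0.88 and 0.68 are yearly event rates, every patient is followed for 2 years, and the design effect of 1.4 carries over from proportions to counts. Using a Wald test on the log rate ratio, with k the negative-binomial dispersion (k = 0 is Poisson):

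n = 1.4 × 8.98 × [1/(2 × 0.88) + 1/(2 × 0.68) + 2k] / ln(0.88/0.68)²

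Here 1/1.76 + 1/1.36 = 1.3035 and ln(0.88/0.68)² = 0.2578² = 0.0665.

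| Dispersion k (assumed) | Needed per arm | Power at 100 per arm |
|---|---|---|
| 0 (Poisson) | 246 | 48% |
| 0.5 | 436 | 30% |
| 1 | 625 | 22% |
| 2 | 1003 | 16% |

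**Step 5. Planning event against primary outcome.** Under Definitions, an ED visit is a consultation without admission. A combined rate of ED visits or admissions therefore cannot be lower than the admission rate, and exceeds it whenever there are ED visits. In the formula above, a lower baseline rate at the same rate ratio and dispersion enlarges the bracket and lowers power.

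**The case against.** The strongest defence is that nothing was miscalculated. Both endpoints, 88% and 68%, are printed, and the size and power follow from them. This is correct: the fault lies in the inputs and the scale, not in the calculation. It also means that the 20% wording is a lesser point. The calculation consistently uses 20 points, and the 70.4% figures show the cost of the other reading, not a mistake in the stated size.

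A second defence is that Analysis of primary outcome plans a binomial model, so a binomial sample size matches the analysis. It does not rescue the 88%. Under Poisson variation, a mean of 0.88 events per year implies 1 − exp(−0.88) = 58.5% of patients with an event in one year. Over 2 years the proportions would be 1 − exp(−1.76) = 82.8% vs 1 − exp(−1.36) = 74.3%, and power at 71.4 effective patients per arm about 24%.

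Stronger readings are tempting but not supported:

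- A reader might take 48% as a ceiling on the trial's true power. That requires 0.88 to be a genuine event rate, which Step 1 gives no ground for; it is an illustration only.
- A reader might take 11% as the true baseline proportion and, with a 20% relative cut to 8.8%, compute about 6% power. The article does not state the period over which 11% of patients presented. If the 11% is assumed annual and compounded to 20.8% over 2 years, against 16.6%, the figure becomes about 9%. Neither can be a headline.
- The dispersion values are not in the article. They are assumptions, so only the range is informative.

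Finally, recruitment was completed in June 2014, so the sample cannot be changed by this point. That limits the remedy to the text and does not make the stated power correct.

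**Conclusion.** The concern holds as a fault of inputs and scale. A share of patients was evidently multiplied by an attack rate, and the result was used as a binomial proportion for an outcome defined as a count. The 100 per arm and roughly 85% power reproduce only on that footing, so the 85% claim is not supported for the primary outcome.

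The true power cannot be calculated from the article, because it gives no admissions-only rate and no dispersion. Under the assumptions of Step 4, the shortfall would be large: 48% with Poisson variation, falling to 16% at dispersion 2. It would be larger still with an admissions-only baseline at the same rate ratio. The mismatch between 20% and 68% is a secondary inconsistency, worth about 10 points of power even on the protocol's own scale.

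**What to change.** Remove the 85% power claim and the 88% and 68% proportions. Restate the calculation on the count scale with:

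- a baseline rate of admissions for angioedema attacks per patient-year, labelled as an assumption with a range, because the article gives only a combined figure for ED visits or admissions;
- the effect as a rate ratio, stated clearly as relative (0.80 for a 20% cut; 0.68/0.88 = 0.77 if the printed endpoints were meant);
- 2 years of follow-up, a range of overdispersion, and the cluster design effect.

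Then report the power that 200 patients give across that range, so that a null result can be read against it. The cost is a rewritten paragraph, outside data or a reasoned assumption for the admission rate, and probably a less favourable power figure. No extra patients are needed.
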